## **7 DISCONTINUATION OF STUDY TREATMENT AND PATIENT DISCONTINUATION/WITHDRAWAL**

Refer the Master AGILE protocol section 7.0

## **8 STUDY ASSESSMENT AND PROCEDURES**

### **8.1 SCREENING PROCEDURES**

Screening procedures to be carried out up to 1 day prior to randomisation and include:

- Informed Consent
- Eligibility Assessment
- Assessment using the WHO Clinical Progression Scale (WHO, 2020):
  0. Uninfected, no viral RNA detected
  1. Ambulatory mild disease, asymptomatic; viral RNA detected
  2. Ambulatory mild disease, symptomatic; independent
  3. Ambulatory mild disease, symptomatic; assistance needed
  4. Hospitalised moderate disease, no oxygen therapy (If hospitalised for isolation only, record stats as for ambulatory patient)
  5. Hospitalised moderate disease, oxygen by mask or nasal prongs
  6. Hospitalised severe disease, oxygen by NIV or high flow
  7. Hospitalised severe disease, intubation and mechanical ventilation  $pO_2/FiO_2 \geq 150$  or  $SpO_2/FiO_2 \geq 200$

8. Hospitalised severe disease, mechanical ventilation  $pO_2/FiO_2 < 150$  ( $SpO_2/FiO_2 < 200$ ) or vasopressors
  9. Hospitalised severe disease, mechanical ventilation  $pO_2/FiO_2 < 150$  and vasopressors, dialysis, or ECMO
  10. Dead
- Non-Ventilated Patients: National Early Warning Score 2 (NEWS2) Assessment:
    - Respiration rate
    - Oxygen saturation
    - Systolic blood pressure
    - Pulse rate
    - Level of consciousness or new confusion\*
    - Temperature

\*The patient has new-onset confusion, disorientation and/or agitation, where previously their mental state was normal – this may be subtle. The patient may respond to questions coherently, but there is some confusion, disorientation and/or agitation. This would score 3 or 4 on the GCS (rather than the normal 5 for verbal response), and scores 3 on the NEWS system.
  - 12 lead ECG and 10 second ECG rhythm strip ( $\geq 5$  min supine), to be performed during screening, or on baseline day 1 prior to first dose.
  - Full blood count
  - Urea and electrolytes
  - Estimated GFR
  - Liver Function Tests
  - Uric acid
  - Urinary analysis
  - Women of childbearing potential: Pregnancy test (serum)
  - Medical history (including COVID-19 history e.g. symptom onset)
  - Concomitant medication and standard of care review
  - Height/supine length and weight (*to be performed during screening, or on baseline day 1 prior to first dose. Can be taken from current admission.*)
  - Assessment of oxygen use (low flow, high flow)
  - Assessment of mechanical ventilation use (Only if supplemental oxygen not being administered, lowest oxygen saturation over the last 24 hours to be recorded as part of baseline/screening)
  - Demographics review
  - Adverse Event Assessment (from consent)
  - Targeted Physical examination

The following assessment, listed in the Master Protocol, is not required at screening in this candidate specific trial protocol:

- Ventilated Patients: Quick Sepsis-Related Organ Dysfunction Assessment (qSOFA) Score

## 8.2 TRIAL PROCEDURES

Participants will receive treatment up to 7 days when hospitalised for COVID-19 and cease when they have been discharged from hospital. Visits outlined in the schedule of events will take place as in-patients when in hospital or out-patient. If discharged participants are not able to return after discharge for clinic visits, follow-up should be done by phone call to the patient and a

minimised criteria will apply to perform AE assessment, concomitant medication and patient status.

**Note that this CST visit schedule differs from the Master Protocol and is the schedule to be used for all patients enrolled onto this candidate specific trial.**

### **8.2.1 Baseline Visit (Day 1, day of randomisation)**

The following assessments are to be carried out on the day of randomisation. Patients should commence treatment on the day of randomisation (i.e. Day 1).

- Assessment using the WHO Clinical Progression Scale (WHO, 2020):
  0. Uninfected, no viral RNA detected
  1. Ambulatory mild disease, asymptomatic; viral RNA detected
  2. Ambulatory mild disease, symptomatic; independent
  3. Ambulatory mild disease, symptomatic; assistance needed
  4. Hospitalised moderate disease, no oxygen therapy (If hospitalised for isolation only, record stats as for ambulatory patient)
  5. Hospitalised moderate disease, oxygen by mask or nasal prongs
  6. Hospitalised severe disease, oxygen by NIV or high flow
  7. Hospitalised severe disease, intubation and mechanical ventilation  $pO_2/FiO_2 \geq 150$  or  $SpO_2/FiO_2 \geq 200$
  8. Hospitalised severe disease, mechanical ventilation  $pO_2/FiO_2 < 150$  ( $SpO_2/FiO_2 < 200$ ) or vasopressors
  9. Hospitalised severe disease, mechanical ventilation  $pO_2/FiO_2 < 150$  and vasopressors, dialysis, or ECMO
  10. Dead
- Non-Ventilated Patients: National Early Warning Score 2 (NEWS2) Assessment:
  - Respiration rate
  - Oxygen saturation
  - Systolic blood pressure
  - Pulse rate
  - Level of consciousness or new confusion\*
  - Temperature

\*The patient has new-onset confusion, disorientation and/or agitation, where previously their mental state was normal – this may be subtle. The patient may respond to questions coherently, but there is some confusion, disorientation and/or agitation. This would score 3 or 4 on the GCS (rather than the normal 5 for verbal response), and scores 3 on the NEWS system.

Vital Signs are collected prior to dose administration, + 30 minutes, end of infusion +1 hour post infusion for Dose 1 only.

- Concomitant medication and standard of care review
- Assessment of oxygen use (low flow, high flow)
- Assessment of mechanical ventilation use ((Only if supplemental oxygen not being administered, lowest oxygen saturation over the last 24 hours to be recorded as part of baseline/screening))
- Adverse event assessment
- SARS-CoV-2 nose/throat swab for storage for future translational research
- SARS-CoV-2 surveillance NP swab

- Chest X-Ray (if clinically indicated)

In addition, for candidate specific trial protocol the following are required:

- Review inclusion and exclusion criteria and confirm eligibility
- Randomisation
- The following is required if not performed within 24 hours of Baseline (*results are required prior to dosing only if clinically indicated*):
  - Full blood count
  - Urea and electrolytes
  - Estimated GFR
  - Liver Function Tests
  - Uric acid
  - Urinary analysis
- Pre-Dose Blood collection for translational research
- Blood samples for PK (Blood and dried blood spot) - Day 1 timepoints of pre-dose, 0-1 hr, 2-4 hr and 6-12 hr post completion of first infusion
- Non-plasma (tears, saliva, nasal secretions) – Day 1 timepoints of 6-12 hr post completion of the first infusion
- PBMC sample - Day 1 timepoints of 6-12 hr post completion of first infusion
- Safety bloods (if clinically indicated)
- Drug administration of Favipiravir (or placebo for Phase II) IV BID dose for 7 days, by infusion over up to 1 h, to be administered in hospital
- Targeted physical examination

### 8.2.2 Treatment

#### Phase I

Participants will be randomised to receive IV Favipiravir or SoC only (2:1) on Day 1. Refer to section 6 of the CST6 protocol for further information.

#### Phase II

Participants will be randomised to receive IV Favipiravir or saline placebo (alongside SoC) on Day 1. Refer to section 6 of the CST6 protocol for further information.

**8.2.3 Daily Day 2 through to Day 14:** when in hospital or via telephone contact if leaves hospital before day 8 to document: adverse events and concomitant medication. First 5 days of treatment, daily SARS-CoV-2 surveillance NP swab. The following as per SoC and if clinically indicated if in hospital:

- Full blood count, U&Es, Uric acid, estimated GFR, LFTs
- Vital signs
- Assessment of oxygen use
- Targeted physical exam

### 8.2.4 Specific Assessments on Days 3, 5, 8 and 11 ( $\pm 1$ day)

The following assessments are to be carried out on 3, 5, 8 and 11 (NB day of randomisation and start date of treatment is Day 1).

- SARS-CoV-2 surveillance NP swab
- Full blood count
- Urea and electrolytes

- Estimated GFR
- Liver Function Tests
- Uric acid
- Concomitant medication and standard of care review
- AE assessment
- Translational swab (Days 3 and 5 only)

In addition, for CST6 candidate specific trial protocol the following are required:

- Assessment using the WHO Clinical Progression Scale (WHO, 2020):
  0. Uninfected, no viral RNA detected
  1. Ambulatory mild disease, asymptomatic; viral RNA detected
  2. Ambulatory mild disease, symptomatic; independent
  3. Ambulatory mild disease, symptomatic; assistance needed
  4. Hospitalised moderate disease, no oxygen therapy (If hospitalised for isolation only, record stats as for ambulatory patient)
  5. Hospitalised moderate disease, oxygen by mask or nasal prongs
  6. Hospitalised severe disease, oxygen by NIV or high flow
  7. Hospitalised severe disease, intubation and mechanical ventilation  $pO_2/FiO_2 \geq 150$  or  $SpO_2/FiO_2 \geq 200$
  8. Hospitalised severe disease, mechanical ventilation  $pO_2/FiO_2 < 150$  ( $SpO_2/FiO_2 < 200$ ) or vasopressors
  9. Hospitalised severe disease, mechanical ventilation  $pO_2/FiO_2 < 150$  and vasopressors, dialysis, or ECMO
  10. Dead
- Non-Ventilated Patients: National Early Warning Score 2 (NEWS2) Assessment:
  - Respiration rate
  - Oxygen saturation
  - Systolic blood pressure
  - Pulse rate
  - Level of consciousness or new confusion\*
  - Temperature

\*The patient has new-onset confusion, disorientation and/or agitation, where previously their mental state was normal – this may be subtle. The patient may respond to questions coherently, but there is some confusion, disorientation and/or agitation. This would score 3 or 4 on the GCS (rather than the normal 5 for verbal response), and scores 3 on the NEWS system.
- Assessment of oxygen use (low flow, high flow, mechanical flow, mechanical ventilation use) (only if supplemental oxygen is not administered) – daily whilst in hospital
- Targeted Physical examination
- Blood (plasma and DBS) taken for PK assessments on Day 3 (pre-dose, 0-1 hr, 2-4 hr, 6-12 hr post completion of first infusion) and Day 5 (0-1hr, 6-12 hr post completion of first infusion)
- Tears, saliva, nasal swab PK assessments - Day 3 timepoints at 6-12 hr post completion of first infusion
- PBMC sample - Day 3 & Day 5 timepoints at 6-12 hr post completion of first infusion
- Blood taken for translational research

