| Secondary Trial Endpoints: | 
Phase I:
 
 
• Plasma PK parameters of Favipiravir up to Day 8
 
• Change from baseline over time, up to Day 29, in viral load
 
• WHO Clinical Progression Scale at day 15 and 29
 
• Mortality at Days 15 and 29
 
• Time from randomisation to death (up to day 29)
 
 
Phase II:
 
 
• AEs, SAEs, physical findings, vital signs and laboratory parameters
 
• Plasma PK parameters of IV Favipiravir up to Day 8
 
• Change from baseline over time, up to Day 29, in viral load
 
• Time to negative viral titres (Day 1-29)
 
• Time to and proportion of clinical improvement. Improvement will be determined according to the WHO Clinical Progression Scale (WHO, 2020); improvement is defined as a minimum 2-step change from randomisation in the scale up to day 29 post-randomisation:
 
• Proportion of patients with clinical improvement (as defined above) at day 8, 15 and day 29
 
• Change at day 8 and 15 from randomisation in the WHO Clinical Progression Scale (WHO, 2020)
 
• Time to a one point change on the WHO Clinical Progression Scale (WHO, 2020)
 
• To evaluate the time to, and proportion of discharge:
 
• Time to discharge from randomisation
 
• Proportion of patient discharged by days 8, 15 and 29
 
• To evaluate overall mortality:
 
• Mortality at Days 8, 15 and 29
 
• Time to death from randomisation
 
• Duration (days) of oxygen use and oxygen free days
 
• Incidence of new mechanical ventilation use and duration (days) of new mechanical ventilation use
 
 |

|                               |                                                                                                                                                                                                                                                                                                                                                                                                                                                                                 |

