| Assessment of oxygen use (low flow, high flow, mechanical ventilation) | X h          | X h      | X h                             |                                                       | X (if hospitalised) |                     |
| Targeted physical exam                                                 | X                       | X                   | X                                          | X                                                     | X                   | X                   |
| Chest X-ray/other chest imaging                                        | If clinically indicated |                     |                                            |                                                       |                     |                     |
| Blood collection for translational research                            |                         | X
(pre dose)     |                                            | X                                                     | X                   | X                   |
| End of study                                                           |                         |                     |                                            |                                                       |                     | X                   |

a. Can be conducted on Day 1 but must be prior to randomisation to confirm eligibility

b. Additional week 24 telephone consultation for pregnancy follow up if female participants became pregnant.

c. Day 3 and 5 only.

d. Results are required prior to dosing only if clinically indicated

e. PK sampling for Phase I: Day 1 (pre-dose, 0-1 hr, 2-4 hr and 6-12 hr post completion of first infusion), Day 3 (pre-dose, 0-1 hr, 2-4 hr and 6-12 hr post completion of first infusion) and at Day 5 (0-1 hr and 6-12 hr post completion of the first infusion). **NOTE:** 6-12 hours post infusion must be taken prior to second infusion

f. Non-plasma PK sampling for Phase I: tears, saliva, nasal collections Day 1 and Day 3 (6-12 hours post completion of infusion)

g. Intracellular (PBM) sampling for Phase I: Day 1 and Day 3 (6-12 hr post completion of first infusion) and at Day 5 (6-12 hr post completion of the first infusion)

h. If supplemental oxygen not being administered, lowest oxygen saturation over the last 24 hours to be recorded as part of baseline/screening

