| 
Clinical objectives:
 
To compare the effect of IV Favipiravir versus placebo on overall mortality, time to discharge, duration of oxygen use (and oxygen free days) and incidence and duration of new mechanical ventilation use
 
To evaluate time to, and proportion of, clinical improvement (WHO clinical progression scale).
 | 
 
• Mortality at Days 8, 15 and 29 (Time to death from randomisation)
 
• Proportion of patient discharged by days 8, 15 and 29 (Time to discharge from randomisation)
 
• Duration (days 1 - 7) of oxygen use and oxygen-free days.
 
• Duration (days) of mechanical ventilation
 
• Incidence of new mechanical ventilation use and duration (days) of new mechanical ventilation use.
 
• Change from baseline over time, up to Day 29, in viral load
 
• Time to negative viral titres (Day 1-29)
 
• Time to and proportion of clinical improvement. Improvement will be determined according to the WHO Clinical Progression Scale (WHO, 2020); improvement is defined as a minimum 2-
 
 |

|                                                                  |                                                                                                                                                                                                                                                                                                                                                                                                                                        |
|------------------------------------------------------------------|----------------------------------------------------------------------------------------------------------------------------------------------------------------------------------------------------------------------------------------------------------------------------------------------------------------------------------------------------------------------------------------------------------------------------------------|

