### 8.2.5 Day 15 ( $\pm 2$ Days)

The following assessments are to be carried out on Day 15 ( $\pm 2$  days) (NB day of randomisation and start date of treatment is Day 1). This differs from the Master protocol as +1 day is permitted to this visit date.

- SARS-CoV-2 surveillance NP swab
- Assessment using the WHO Clinical Progression Scale (WHO, 2020):
  0. Uninfected, no viral RNA detected
  1. Ambulatory mild disease, asymptomatic; viral RNA detected
  2. Ambulatory mild disease, symptomatic; independent
  3. Ambulatory mild disease, symptomatic; assistance needed
  4. Hospitalised moderate disease, no oxygen therapy (If hospitalised for isolation only, record stats as for ambulatory patient)
  5. Hospitalised moderate disease, oxygen by mask or nasal prongs
  6. Hospitalised severe disease, oxygen by NIV or high flow
  7. Hospitalised severe disease, intubation and mechanical ventilation  $pO_2/FiO_2 \geq 150$  or  $SpO_2/FiO_2 \geq 200$
  8. Hospitalised severe disease, mechanical ventilation  $pO_2/FiO_2 < 150$  ( $SpO_2/FiO_2 < 200$ ) or vasopressors
  9. Hospitalised severe disease, mechanical ventilation  $pO_2/FiO_2 < 150$  and vasopressors, dialysis, or ECMO
  10. Dead
- Non-Ventilated Patients: National Early Warning Score 2 (NEWS2) Assessment:
  - Respiration rate
  - Oxygen saturation
  - Systolic blood pressure
  - Pulse rate
  - Level of consciousness or new confusion\*
  - Temperature

\*The patient has new-onset confusion, disorientation and/or agitation, where previously their mental state was normal – this may be subtle. The patient may respond to questions coherently, but there is some confusion, disorientation and/or agitation. This would score 3 or 4 on the GCS (rather than the normal 5 for verbal response), and scores 3 on the NEWS system.
- Full blood count
- Urea and electrolytes
- Estimated GFR
- Liver Function Tests
- Uric acid
- Concomitant medication and standard of care review
- AE assessment
- Assessment of oxygen use (low flow, high flow, mechanical flow, mechanical ventilation use) (only if supplemental oxygen is not administered) – daily whilst in hospital
  - Chest X-Ray (if clinically indicated)

In addition, for candidate specific trial protocol the following are required:

- Targeted physical exam
- Blood collection for translational research

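### Sections 8.2.4 and 8.2.5 ask for oxygen and ventilation use only when oxygen is not being given, contradicting the schedule, and the windows of the endpoints that need these data are not settled

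*Protocol*

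**What the plan says.** **Visit text.** Section 8.2.4 (Days 3, 5, 8 and 11) lists "Assessment of oxygen use (low flow, high flow, mechanical flow, mechanical ventilation use) (only if supplemental oxygen is not administered" and extends the rule beyond those visits: "only if supplemental oxygen is not administered) – daily whilst in hospital". Section 8.2.5 (Day 15) repeats the condition: "mechanical ventilation use) (only if supplemental oxygen is not administered".

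**Schedule.** In section 1.3 the row "Assessment of oxygen use (low flow, high flow, mechanical ventilation" is marked at screening, Day 1, daily in hospital on Days 2-14, and on Day 15 for those still in hospital. It is blank under Days 3, 5, 8 and 11 and under Day 29. Footnote h reads: "If supplemental oxygen not being administered, lowest oxygen saturation over the last 24 hours to be recorded as part of baseline/screening". It adds a saturation record; it does not limit the oxygen-use assessment.

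**Screening and baseline.** In sections 8.1 and 8.2.1 the oxygen-use item has no condition. The condition appears under the ventilation item and applies to the saturation record: "Only if supplemental oxygen not being administered, lowest oxygen saturation over the last 24 hours to be recorded".

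**Days 2-14.** Section 8.2.3 lists oxygen use among items done according to usual care and clinical need.

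**Endpoints.** Section 3.2 has "Duration (days 1 - 7) of oxygen use and oxygen-free days"; the synopsis has "Duration (days) of oxygen use and oxygen free days", with no window. Incidence and duration of new ventilation have no window in either place. Section 3.2 also lists the duration of mechanical ventilation overall, which the synopsis omits.

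**The concern.** The condition in 8.2.4 and 8.2.5 is the reverse of what the endpoints need. Grades 5 and 6, two of the three entry grades, are on oxygen by definition. A site working from the visit text would leave the item blank for such a patient until oxygen stopped. Whether a day is recorded would then depend on the outcome being measured. A blank could mean oxygen was given, the assessment was missed or the patient had gone home, and the type of support would be lost.

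At stake are the Phase II secondary endpoints on duration of oxygen use, oxygen-free days, and incidence and duration of ventilation. The synopsis names these outcomes in its Phase II secondary objectives. The unsettled window adds to the problem because it determines what must be collected prospectively. It cannot all be left to the analysis stage.

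**Working it through.** The protocol gives no figure to reproduce here. The check sets the recording rules side by side and counts the days each covers.

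| Source | When oxygen and ventilation use is recorded | Depends on oxygen status? |
|---|---|---|
| 1.3 schedule row | Screening, Day 1, daily in hospital Days 2-14, Day 15 if in hospital | No |
| 8.1 and 8.2.1, oxygen item | Screening and Day 1 | No |
| 8.2.3 | Days 2-14 in hospital, per usual care and clinical need | No, but not mandatory |
| 8.2.4 | Days 3, 5, 8, 11, and daily in hospital | Yes: only when oxygen is not given |
| 8.2.5 | Day 15, and daily in hospital | Yes: only when oxygen is not given |

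**Step 1: which rule governs?** The protocol does not say. Section 8.2 states that this trial's visit schedule replaces the Master Protocol's, so the Master's schedule is no fallback. It does not rank section 1.3 against 8.2.3-8.2.5.

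**Step 2: the Days 1-7 window in 3.2.** Under the schedule, Day 1 plus Days 2-7 gives 1 + 6 = 7 of 7 days for a patient in hospital throughout. Under 8.2.4 read literally, days on oxygen after Day 1 are not assessed. Under 8.2.3, coverage depends on local practice.

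**Step 3: can the WHO scale fill the gap?** It is recorded without any oxygen condition at screening and on Days 1, 3, 5, 8, 11, 15 and 29, and Grades 5-9 separate oxygen, NIV or high flow, and ventilation. Nominal Days 1-7 contain three of these visits (Days 1, 3 and 5), leaving 7 - 3 = 4 days without a grade. The scale shows support at a visit, but it cannot give a duration in days and can miss an episode between visits. Ambulatory Grades 1-3 have no oxygen category.

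**Step 4: a longer window.** The synopsis gives none. If it were taken as Days 1-29 (an assumption, matching the length of follow-up), scheduled oxygen recording stops at Day 15. Days 16-29 are 29 - 15 = 14 days, or 14/29 = 48% of the span, with only the Day 29 WHO grade. A patient first ventilated on Day 17 and extubated before Day 29 would have no scheduled ventilation record.

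**Step 5: after discharge.** The calls in 8.2.3 cover adverse events and concomitant medication. Section 8.2 adds an undefined patient status when a clinic visit is not possible. Neither asks about oxygen.

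**The case against.** The strongest reply is that this is a wording slip that the schedule already resolves. An item that lists low flow, high flow and ventilation cannot sensibly be meant only for patients off oxygen. The parenthesis looks like a truncated footnote h, and a site following section 1.3 would record every in-patient day of the only window the protocol states. The 7-day window also matches the treatment period. These are secondary endpoints.

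Much of this stands. A reader might infer that the endpoints cannot be computed, or that every day on oxygen goes unrecorded. The documents do not support that: screening, Day 1 and the schedule carry no such restriction, and the WHO grade is unconditional. The stronger reading requires 8.2.4 and 8.2.5 to override the schedule, which the protocol nowhere says.

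A reader might also infer that a 7-day window cuts off most of the oxygen course, or that Day 29 is the required horizon. The protocol gives no figure for oxygen duration and sets no Day 29 horizon for these outcomes. How deaths count in durations or oxygen-free days is properly left to the statistical analysis plan, which is not shown; nothing in the protocol settles it wrongly.

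What the reply does not remove is that three recording rules are in force without precedence, one of them reversed and stated twice. An implausible instruction can still be followed, or built into a case report form.

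**Conclusion.** The point holds as an internal contradiction with a practical consequence. Sections 8.2.4 and 8.2.5 state a recording rule that, if followed, loses on-oxygen days the Phase II secondary endpoints must count. It conflicts with the schedule, and 8.2.3 conflicts with both. The endpoint window differs between 1.1 and 3.2 and is absent for ventilation.

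The size depends on which text sites follow. Under the schedule, in-patients have all 7 days of the Days 1-7 window. Under the visit text, the loss could reach every in-hospital day on oxygen after Day 1, though the WHO grade would still be taken at fixed visits. For a Day 29 span, which is an assumption, 14 of 29 days have only the Day 29 WHO grade whichever rule is followed.

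The viral-load primary endpoint, the interim rules and the sample size are unaffected. The text should be corrected before Phase II collection, because unrecorded days may not be fully recoverable later.

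**What to change.** 1. In 8.2.4 and 8.2.5, delete the parenthesis that makes the assessment conditional on oxygen not being given, so that oxygen and ventilation use is recorded daily in hospital regardless of oxygen status.
2. Keep the lowest-saturation record as a separate screening and baseline item. Do not copy footnote h into 8.2.4 or 8.2.5, since its wording concerns screening and baseline.
3. Align 8.2.3 with the daily entry in the schedule.
4. State one window for the oxygen and ventilation endpoints, in the same words in 1.1 and 3.2. Its length is the sponsor's choice.
5. Make recording cover that window, including days after discharge. If it runs past Day 15, collect start and stop dates of each type of support from hospital records.

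The cost is a protocol wording change, a check that the case report form does not carry the condition, and a small amount of extra data entry, mainly for patients still in hospital after Day 15 if the longer window is chosen.
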